## Abstract

**Background:**

Premature birth poses significant health challenges globally, impacting infants, families, and society. Despite recognition of its contributing factors, efforts to reduce its incidence have seen limited success. A notable gap exists in the awareness among women of childbearing age (WCA) regarding both the risks of premature birth and the preventative measures they can take. Research suggests that enhancing health beliefs and self-management efficacy in WCA could foster preventive health behaviors. Interactive webtoons offer an innovative, cost-effective avenue for delivering engaging, accessible health education aimed at preventing premature birth.

**Objective:**

This protocol describes a randomized controlled trial to assess the effectiveness and feasibility of a novel, self-guided, web-based intervention—Pregnancy Story I Didn’t Know in Interactive Webtoon Series (PSIDK-iWebtoons)—designed to enhance self-management efficacy and promote behaviors preventing premature birth in WCA.

**Methods:**

Using an explanatory sequential mixed methods design, this study first conducts a quantitative analysis followed by a qualitative inquiry to evaluate outcomes and feasibility. Participants are randomly assigned to 2 groups: one accessing the PSIDK-iWebtoons and the other receiving Pregnancy Story I Didn’t Know in Text-Based Information (PSIDK-Texts) over 3 weeks. We measure primary efficacy through the self-management self-efficacy scale for premature birth prevention (PBP), alongside secondary outcomes including perceptions of susceptibility, severity, benefits, and barriers based on the health belief model for PBP and PBP intention. Additional participant-reported outcomes are assessed at baseline, the postintervention time point, and the 4-week follow-up. The feasibility of the intervention is assessed after the end of the 3-week intervention period. Outcome analysis uses repeated measures ANOVA for quantitative data, while qualitative data are explored through content analysis of interviews with 30 participants.

**Results:**

The study received funding in June 2021 and institutional review board approval in October 2023. Both the PSIDK-iWebtoons and PSIDK-Texts interventions have been developed and pilot-tested from July to November 2023, with the main phase of quantitative data collection running from November 2023 to March 2024. Qualitative data collection commenced in February 2024 and will conclude in May 2024. Ongoing analyses include process evaluation and data interpretation.

**Conclusions:**

This trial will lay foundational insights into the nexus of interactive web-based interventions and the improvement of knowledge and practices related to PBP among WCA. By demonstrating the efficacy and feasibility of a web-based, interactive educational tool, this study will contribute essential evidence to the discourse on accessible and scientifically robust digital platforms. Positive findings will underscore the importance of such interventions in fostering preventive health behaviors, thereby supporting community-wide efforts to mitigate the risk of premature births through informed self-management practices.

**Trial Registration:**

Korea Disease Control and Prevention Agency (KDCA) KCT0008931; https://cris.nih.go.kr/cris/search/detailSearch.do?seq=25857

**International Registered Report Identifier (IRRID):**

DERR1-10.2196/58326

## Introduction

### Background

Premature birth is defined as a live birth that occurs before 37 weeks of pregnancy. The estimated global premature birth rate per 100 live births was 9.9% (13.4 million premature births) in 2020 [1]. It poses a serious health issue for children, their families, and society worldwide [2], with complications from premature birth being the primary contributors to childhood mortality. This accounts for 35% of all deaths during the neonatal period and 18% of all deaths in children younger than 5 years [3]. Premature birth is also associated with short-term and long-term morbidity, developmental loss in children, adult-onset diseases, and negative impacts on human capital, such as lower education and income levels and reduced social success [2].

A variety of community, societal, maternal, and fetal health factors affecting premature birth before and during pregnancy have been identified [2]. Interventions including medication, surgical procedures, cervical devices, targeted diets, physical exercise, smoking cessation programs, nutritional supplementation, education, and various special tests or investigations have been developed with reported effectiveness [4,5]. However, despite efforts to reduce its prevalence over the past several decades, the rate of premature birth has not significantly changed, showing a slight increase of 0.14% per year on average from 2010 to 2020 [1]. Women of childbearing age (WCA) still lack awareness about premature birth and the necessary health behaviors to prevent it [6,7]. Research has predominantly focused on the effects of trials with single-pronged interventions targeting narrow aspects, unable to address the complexity of premature birth’s multifactorial etiological network of risk factors [2]. Moreover, step-by-step, long-term interventions are recommended for women both before and during pregnancy, with most intervention development concentrating on pregnant women and neglecting WCA in prepregnancy stages [7].

To prevent premature birth, it is crucial for women to be aware of its risks and to cultivate preventive health behaviors. The health belief model highlights the importance of strengthening health beliefs, which include perceived susceptibility, severity, benefits, and barriers, alongside self-efficacy and behavioral intention, in promoting health behaviors [8]. Studies have shown that health beliefs significantly influence prepregnant [9] and pregnant women [10-13], predicting health behavior. Self-efficacy is a key factor in WCA’s health behaviors before [7,9] and during pregnancy [13]. Thus, enhancing health beliefs and self-efficacy regarding premature birth prevention (PBP) could lead to an increase in preventive health behaviors.

WCA have shown a preference for web-based education for its accessibility and convenience [7]. Systematic reviews have indicated the effectiveness of web-based education programs for WCA both before [14] and during pregnancy [15,16], suggesting web-based interventions as practical and potentially more effective educational tools. Such interventions, adaptable across devices, offer personalized and interactive educational experiences [16]. Moreover, WCA have expressed a preference for case-based education using visuals over text [7].

Webtoons, digital comics, or graphic novels presented in a vertical, scrollable format designed for easy reading on computers and mobile devices contain narrative, image, metaphor, and characterization elements. They are an effective educational method that increases understanding and awareness, easily creates empathy, and engages readers through interactive storytelling [17]. Webtoons have been shown to enhance learners’ interest, concentration, critical thinking, participation, and sharing [17,18]. Their effectiveness in educational interventions, particularly in the context of women’s pregnancy health, has been demonstrated through improvements in actual and perceived knowledge, risk perception, affective assessment, self-efficacy, intention to take protective behaviors, subsequent information-seeking behavior [19], environmental health perceptions, and behaviors during pregnancy [20]. Additionally, webtoons have been effective in increasing self-efficacy and knowledge regarding preventive health management of premature labor among WCA [21]. Therefore, to prepare a new intervention plan that is highly accessible, increases interest and concentration, and allows for participation and sharing to prevent premature birth in WCA, we propose to develop a web-based intervention using webtoons and aim to validate its effectiveness.

### Objectives

This study is designed to evaluate the efficacy and feasibility of “Pregnancy Story I Didn’t Know in Interactive Webtoon Series (PSIDK-iWebtoons),” an interactive web program aimed at preventing premature birth. The efficacy of the intervention will be assessed by comparing self-reported self-management self-efficacy for premature birth prevention (SMSE-PBP), health belief model scale for premature birth prevention (HBM-PBP), and premature birth prevention intention (PBPI) among WCA who receive the PSIDK-iWebtoons intervention to those who receive the text-based version, “Pregnancy Story I Didn’t Know in Text-based Information (PSIDK-Texts).” To explore the feasibility of PSIDK-iWebtoons, we will examine participants’ satisfaction using the Client Satisfaction Questionnaire-8 (CSQ-8) and evaluate the quality of the website, comparing responses between the 2 groups. Additionally, insights into the intervention’s effects and feasibility will be further drawn from a qualitative content analysis based on interviews with participants conducted after the second postintervention period (T2) and from usage data of the intervention recorded through web activity tracking.

## Methods

### Study Design

This study uses an explanatory sequential mixed methods design [22]. Initially, a quantitative study (phase 1) will assess the intervention’s effects and feasibility through a 1:1 parallel-group, superiority, double-blind, randomized controlled trial. Subsequently, phase 2 will involve one-to-one and semistructured interviews to provide deeper qualitative insights.

### Setting

The study will be hosted on a dedicated website titled “Pregnancy Story I Didn’t Know” (Korean: 내가 몰랐던 임신 이야기), with the program referred to as PSIDK-iWebtoons. This platform will be accessible exclusively to invited participants from any region of South Korea, ensuring privacy and control over the study’s environment. A few screenshots of the program displayed on mobile devices are included in Multimedia Appendix 1.

### Inclusion and Exclusion Criteria

Participants will be selected based on the criteria presented in Textbox 1. Participants in this study are WCA who intend to give birth on their own in the future, plan to become pregnant, or are currently in the first trimester of pregnancy, regardless of whether they have high-risk factors for premature birth. Interview participants will be drawn from both the experimental and control groups, focusing on those showing significant changes in main effect variable scores. Approximately 30 participants will be selected for interviews to further explore the intervention’s impact and practicality.

Inclusion and exclusion criteria for the study.
**Inclusion criteria**
Women of childbearing age, ranging from 19 to 49 yearsWomen who express intentions to conceive in the foreseeable future, are actively planning for pregnancy, or are currently in the first trimester of pregnancyBeing able to read and write in KoreanHaving access to an intern-capable device (smartphone, tablet, laptop, or desktop)Possessing a valid phone number and email for website account creationActive user of mobile instant messaging apps or social media, with readiness to use these for study participationWillingness to engage in a self-help web program for 3 weeks and provide written consent for participation
**Exclusion criteria**
Having a previous experience of premature birthHaving a career in a childbirth facility as a health care provider

### Intervention

#### Overview

Participants in both the experimental and comparative groups will access their designated web programs using personal internet devices, such as smartphones, tablets, laptops, or desktops. Over a 3-week period, they will independently register by clicking on a provided link, at their convenience, without set limits on duration or frequency of participation. The approach encourages self-guided engagement with the web programs, adhering to principles of minimal contact.

Three days prior to the intervention’s start, participants will receive an SMS text message on their mobile phone from a research assistant, outlining details about the commencement and procedures for participation. On the morning of the start date, an additional message will provide specific information, including the website address, the participation time frame, account creation instructions, an introduction to the program, learning methodologies, reflection writing guidelines, and a note to prevent account sharing. Further, reminder messages will be sent twice a week (Monday and Thursday) after the intervention begins. Participants found engaging in activities not related to the intervention’s objectives, such as marketing promotions or violating digital etiquette and civility standards, will be subject to removal by the administrator according to the established discontinuation criteria.

#### Experimental Group

##### Overview

Participants in the experimental group will engage with the PSIDK-iWebtoons intervention through the website. Designed as a responsive web application, it aims to improve accessibility across different operating systems and devices, catering to a wide range of users. The intervention includes 7 webtoon series coupled with professional information, and it encourages participants to make comments or provide feedback by writing about their reflections on the webtoon series.

##### Webtoon Series Learning and Repeated Learning

The webtoon series features the stories of 7 women, 6 of whom have high-risk factors for premature birth, spanning from prepregnancy to pregnancy phases, with each story culminating in 3-4 different endings. Participants in the experimental group begin by creating personal accounts and completing questionnaires to identify high-risk factors for premature birth (Textbox 2). Based on the questionnaire responses, a personalized list of recommended webtoon series is generated and prioritized at the top of the web page for easy selection.

Questionnaires on high-risk factors for premature birth.Please respond with “yes” if applicable, “no” if not applicable, or “not sure” by checking the appropriate box next to each of the following risk factors for premature birth.Are you able to manage your pregnancy health effectively on your own?Have you undergone prepregnancy health checkups? Or do you intend to do so?Is your current age or planned age at the time of pregnancy 36 years or older?Were all your pregnancies planned, or do you intend for future pregnancies to be planned?Do you currently smoke?Do you handle stress well, or do you have difficulty managing stress?Do you have many responsibilities, such as work, childcare, and caregiving?Have you had difficulty with nutritional intake or been underweight currently or before pregnancy?Are you currently overweight or obese currently or before pregnancy?Have you experienced premature labor in the past?Have you been trying to conceive for over a year without success, experiencing infertility?Do you currently have high blood pressure, or did you have hypertension during a past pregnancy?Have you been diagnosed with diabetes or gestational diabetes currently or in the past?Do you currently have or have you ever had amniotic fluid leak before 37 weeks of pregnancy?Have you had cervical surgery currently or in the past?Have you experienced early separation of the placenta before childbirth, causing bleeding?Do you currently have excess amniotic fluid, or did you have it in the past?Are you currently pregnant with twins, or have you had a twin or more pregnancies in the past?Are you frequently exposed to chemicals or pesticides?Do you have uterine fibroids (myomas)?

Participants are then guided through an introduction to the program’s objectives and how to navigate the website efficiently. This includes accessing the PBP education page to choose and read from the series recommended to them or from the entire list of webtoon series available. Each story is designed with key learning outcomes in mind and incorporates 2 or 3 decision-making user interfaces that allow participants to direct the actions of the protagonist. The choices made at these decision points alter the course of the story, leading to various endings. Each webtoon series is structured to have 3 or 4 possible outcomes, enriching the learning experience by illustrating the consequences of different health decisions and behaviors.

Participants are unrestricted in their choice of webtoon series from the list, with no limits on viewings, fostering repeated engagement. After finishing a story ending, they are taken to the webtoon list on their “my page,” now updated with a badge marking completion and the completion date. The “my page” learning record will then list the series engaged with, showing high-resolution, clear images for endings they have completed. Conversely, endings that remain unexplored are indicated by blurred images, marked “Incomplete.” These blurred images visually cue participants about content that awaits their attention. An indicator of learning progress is also displayed as a percentage for each ending, allowing for a review of choices made and the option to continue from the last decision point, enhancing the interactive and personalized learning experience.

##### Professional Information Review

Participants in the experimental group have access to detailed professional information linked to the learning content of the webtoons. This information is succinctly summarized and available in 2 formats: “Learn All” and “Learn Selectively.” “Learn Selectively” allows participants to delve into health information pertinent to each individual series upon its completion, while “Learn All” offers comprehensive insights across all series, accessible at any point during the intervention. This structured approach enables participants to either broaden their knowledge base or focus on specific topics of interest.

##### Writing and Sharing Reflections

Following the exploration of each webtoon series, participants are encouraged to write reflections. These reflections prompt them to answer semistructured questions on various aspects, including the main narrative, the most impactful content, learned health behaviors for PBP, strategies for coping with PBP, and areas of confusion or curiosity. Reflections are to be concise, with a length requirement of 30-300 Korean characters (roughly equivalent to 20-200 English words), ensuring focused and meaningful contributions. At least one reflection must be shared publicly, fostering an interactive community environment. Participants can then view and engage with others’ reflections, leaving comments and expressing appreciation through “hearts” (emoticons), further enhancing the communal learning experience.

#### Comparative Group

To maintain the integrity of the study through blinding, a specialized website was developed exclusively for the comparative group. This platform, hosted on TISTORY—a blogging service by Kakao Corp—mimics the layout of conventional websites, featuring primarily text-based content. This choice leverages the ubiquity of KakaoTalk (Kakao Corp), a messaging service dominating 98% of messaging app usage time in Korea, to ensure familiarity and accessibility for participants [23].

Participants in this group will be introduced to the PSIDK-Texts intervention. Unlike their counterparts in the experimental group, who interact with the webtoon series, the comparative group will engage with 7 text-based fictional cases. These narratives mirror the webtoon content available to the experimental group, ensuring content parity across groups. Additionally, they will have access to the same professional information, available in both “Learn Selectively” and “Learn All” formats, aligning with the educational material provided to the experimental group.

The engagement process for the comparative group involves creating a personal account on the TISTORY platform. From there, participants will navigate the intervention autonomously, reading through the case studies and accompanying professional information. They are also encouraged to reflect on their learning by writing and sharing at least one reflection on the platform, mimicking the reflective exercise of the experimental group but within a text-centric learning environment.

Upon the conclusion of the final survey, participants in the comparative group will be granted access to the same educational program that was provided to the experimental group. They will receive the URL, enabling them to benefit from the program at their convenience, thereby ensuring equitable access to the intervention resources after trial.

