### Participant Timeline

Recruitment and intervention delivery for participants are structured over 5 cycles. Each recruitment phase spans 2 weeks, during which interested individuals can sign up and immediately complete a preintervention digital survey. After this period, followed by another 2 weeks, an intervention link is sent via SMS text message 3 days prior to commencement (typically on Friday), signaling the start of a 3-week engagement phase according to each participant’s schedule. Throughout the intervention, SMS text messages from research assistant A are sent twice a week (on days 1, 4, 8, 11, 15, and 18) to encourage ongoing participation. The notification schedule is designed to avoid weekends and provide notifications in the middle of the day. A postintervention survey (T1) invitation is sent via text shortly after the intervention ends, with participants expected to complete this survey autonomously within the following week. After a 4-week washout period, a second postintervention survey (T2) follows a similar process. Subsequently, participants are invited to partake in one-on-one qualitative interviews, conducted on the web by 2 researchers. Each recruitment cycle initiates after the completion of the preceding 2-week recruitment phase. A detailed timeline of enrollment, interventions, assessments, and interviews is illustrated in Figure 1.

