### Blinding

Participants will be informed at the onset that they will be randomly assigned to 1 of 2 web-based interventions, with the design making it challenging for them to discern their assigned intervention. This ensures participants are blinded to their group allocation throughout the intervention, postintervention surveys, and interviews. The comparative group will only be unblinded after completing the interview phase, at which point they will be offered the intervention provided to the experimental group. Research assistant B will be temporarily hired solely for participant allocation, and the other researchers, including research assistant A, will not participate in the allocation process.

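### The protocol gives two different times for opening the webtoons to the comparison group, and under one of them a comparison interviewee could have access, and learn her allocation, before her interview

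*Protocol article*

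**What the plan says.** Two sections of the protocol article fix the time at which the comparison group receives the webtoon programme.

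- **Comparative Group:** "Upon the conclusion of the final survey, participants in the comparative group will be granted access to the same educational program". The next sentence describes how: "They will receive the URL, enabling them to benefit from the program at their convenience".
- **Blinding:** "The comparative group will only be unblinded after completing the interview phase, at which point they will be offered the intervention". The same section says of the blinding: "This ensures participants are blinded to their group allocation throughout the intervention, postintervention surveys, and interviews".

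The Participant Timeline fixes the order of the other events. The last survey is T2: "After a 4-week washout period, a second postintervention survey (T2) follows a similar process". The interviews come next: "Subsequently, participants are invited to partake in one-on-one qualitative interviews, conducted on the web by 2 researchers". The Objectives section also places the interviews after T2.

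Interviewees come from both groups, about 30 in all (Inclusion and Exclusion Criteria; Interview Data). The split between groups is not stated. The Qualitative Outcome section has them asked about perceived change in self-efficacy from before to after the programme, about health beliefs, about satisfaction and about the website.

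**The concern.** The interviews are the second stage of an explanatory sequential design, and their purpose is to help explain what the surveys show. For a comparison interviewee, the questions on change, satisfaction and website quality concern the text programme. If she already has the webtoon link, she may have seen the other programme. Her answers may then be coloured by the comparison, or refer partly to the wrong site. She would also know which arm she was in, which contradicts the statement that blinding lasts through the interviews.

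A second possible effect concerns the webtoon site, where participants share reflections and comment on one another's. If comparison women from an early cycle are let in while a later experimental cycle is still in its intervention period, the two groups could meet on the site.

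**Working it through.** **Order of events for a comparison interviewee**

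| Source | Order |
|---|---|
| Comparative Group | T2, then webtoon access, then interview |
| Blinding | T2, then interview, then webtoon access |

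Both cannot hold for the same woman, and no other section chooses between them.

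**Calendar.** Inputs from Participant Timeline: recruitment 2 weeks, a further 2 weeks before the start, intervention 3 weeks, T1 survey 1 week, gap 4 weeks, T2 survey 1 week; 5 cycles, each starting when the previous 2-week recruitment ends. Inputs from Trial Status: surveys from 6 November 2023 to 31 March 2024; interviews from February to May 2024.

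1. Length of a cycle: 2 + 2 + 3 + 1 + 4 + 1 = 13 weeks.
2. Cycle 1: 6 November 2023 + 13 weeks = 5 February 2024, so T2 closes on about 4 February.
3. Cycle 5 starts 4 × 2 = 8 weeks later, so its T2 closes just before 5 February + 8 weeks = 1 April 2024. This reproduces the stated end of 31 March 2024, which supports the reconstruction.

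**Time available for exposure before interview (upper bounds, interview assumed on 31 May)**

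- Cycle 1: 5 February to 31 May is 116 days, 116 / 7 = 16.6 weeks.
- Cycle 5: 1 April to 31 May is 60 days, 60 / 7 = 8.6 weeks.

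The interval between T2 and a given interview is not stated, so the actual time may be only days.

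**Overlap on the webtoon site, if the final survey means each cycle's own T2**

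- Cycle 5 starts on 6 November + 8 weeks = 1 January 2024. Its intervention begins 4 weeks later, on 29 January, and lasts 3 weeks, to 18 February.
- Cycle 1 access from 5 February overlaps it from 5 to 18 February, the last two weeks.
- Cycle 2 access begins two weeks after cycle 1, on 19 February, after cycle 5 has finished.
- Cycle 4 intervention runs from 15 January to 4 February, so it ends before any access.

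Cycle 1 with cycle 5 is therefore the only overlap. If the final survey means the end of all survey collection on 31 March 2024, every intervention period is over and there is none. Under that reading interviews can still follow access, because they run into May.

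**Number of women concerned.** If the 30 interviews were split evenly (an assumption), 15 would be comparison women. Of the 91 planned for that group (Sample Size), 91 − 15 = 76 would have no interview for access to precede.

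**The case against.** The strongest reply is that the Blinding section already sets the protective rule, in exclusive terms and in the place where a reader would look for it. The sentence under Comparative Group closes with a statement about fair access after the trial, and may be loose shorthand or meant for the women who are not interviewed. On that view this is a drafting slip, not a planned exposure. That is plausible as to intent, but it does not settle which rule applies. Neither section limits itself to interviewees or non-interviewees. Interviewees are also chosen with an eye to change in the main outcome scores. If T2 scores are used, it is not yet known who will be interviewed when a woman completes T2.

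The objection is right about the size of the problem, and several stronger readings should be set aside.

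- A reader might infer that comparison interviewees will have used the webtoons. The documents support only that they could have: they receive a link and use is optional.
- A reader might take all 15 or so comparison interviewees as affected, for up to 16 weeks. The first figure assumes an even split and exposure of every one of them; the second assumes a cycle 1 woman interviewed at the end of May, although interviews began in February, when cycle 1 T2 closes.
- A reader might infer that such interviews no longer describe the text programme. Later access may colour recall, but it does not erase three weeks with that programme, whose cases mirror the webtoon content and whose professional information is the same.
- A reader might infer general mixing of early and late cycles. The calendar allows one two-week overlap, under one of two readings.

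**Conclusion.** The contradiction is real and unresolved in the protocol article. If the Comparative Group rule is followed, the stated blinding through the interviews fails for any comparison woman who is sent the link before her interview, and her account of the text programme could be affected. The effect is confined to the comparison-group part of about 30 interviews, and its actual extent cannot be derived from the document.

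A reader might go further and infer that the efficacy comparison is compromised because the control group crosses over. The document does not support that. Each woman's own T0, T1 and T2 surveys, including the primary self-efficacy scale, are collected before her access under either rule. The one remaining route to the quantitative data is the overlap of cycle 1 access with the last two weeks of the cycle 5 intervention. It requires that the final survey means each cycle's own T2 and that the comparison women enter the same live site. It is a secondary point.

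The correction is worth making because it costs little and protects the purpose of the qualitative stage.

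**What to change.** Amend the Comparative Group section to agree with the Blinding section, and state the access time relative to both T2 and the interview:

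- for comparison women selected for interview, webtoon access starts only after their own interview;
- for the other comparison women, access starts not before survey collection and the selection of interviewees are both complete. This also removes the possible overlap with cycle 5.

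Trial Status reports that surveys have ended and interviews have begun, so a change of timing cannot reach women who already have the link. For interviews already held, record the date on which each comparison interviewee was given access, and flag any interview that took place after it when the qualitative results are reported.

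The cost is a revised sentence, one date per comparison interviewee, and a short delay of access for some comparison women.
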